### Training

Training of a minimum of 80% of relevant nursing and medical staff within the two NICUs will commence in the 6 months prior to study start. This figure has been chosen, based on guidance from senior NICU clinicians and nursing staff, to ensure that there will always be staff members on-shift who are trained to undertake the assay throughout the study.

Training will include practical use and interpretation of the assay, with Standard Operating Procedures for use integrated into the standard admission procedure. A ‘train the trainer’ approach will be adopted, where a number of experienced NICU research nurses plus additional clinical nursing staff identified as ‘super-users’ will receive training directly from representatives of the device manufacturer. These designated super-users will then cascade training to the remaining nursing and medical staff within the two neonatal services.

Ongoing refresher training and online resources will be made available throughout the trial. A training log will be maintained detailing staff competency including dates of training, in order to identify any correlation of assay performance with increasing training numbers. NICU research nurses and coinvestigators will be fully Good Clinical Practice (GCP) competent. A local, named coinvestigator (neonatal consultant) will be responsible for clinical staff performing any duties in accordance with the protocol, GCP and local requirements.

### Testing process and assessment

Participants will be recruited as they are admitted or reviewed by the NICU team. Given the acute nature of the project and the timeframes involved, there is no opportunity to undertake a formal pretrial screening assessment or prospective consenting process. All babies admitted to NICU or screened for infection by the NICU team will be deemed eligible for recruitment unless there is a clinical decision by the responsible admitting clinician that the exclusion criterion is met and the individual requires immediate antibiotic therapy, without delay.

Following recruitment, the time that a decision was made to prescribe antibiotics represents time 0 (figure 1). If antibiotics were not prescribed, then time 0 is represented by the time of admission. The genetic POCT is performed from a buccal swab. When babies are admitted to NICU several swabs are already taken at admission. Where babies are recruited to the study, the m.1555A>G buccal swab will be performed alongside these normal admission processes. The assay will be commenced, and normal practice will continue. Once the assay result is available, it can be used to then undertake personalised antibiotic prescribing, avoiding aminoglycoside antibiotics if the m.1555A>G variant is detected. The CE certified assay will be integrated into the admission pathways at both centres and clinicians will not be blinded to the results.

**Figure 1 F1:**
[figure not shown]
Flow diagram demonstrating the admission, testing and prescribing process in the Pharmacogenetics to Avoid Loss of Hearing trial. The time that a decision was made to prescribe antibiotics represents time 0. If antibiotics were not prescribed, then time 0 is represented by the time of admission. POCT, point of care test.

As part of the study the following variables will be recorded; participant demographics, admission time, time of decision to prescribe, time swab taken, time assay started, time of assay result, assay result, time of antibiotic prescription, antibiotics prescribed. Where a positive result is identified and antibiotic therapy is required, an alternative antibiotic regimen (standard non-gentamicin pathway as per hospital guidelines) will be prescribed and a referral should be made to clinical genetics for familial cascade testing. Where there is a test-fail, standard of care should be followed, that is, the baby should be administered gentamicin if clinically indicated. Negative results will not be formally reported to the parents. However, all parents will be provided with information on the study in their information pack, allowing them to contact the study team for further information if they wish.

Assay performance will be assessed throughout the study, with at least 10% of samples each month tested via gold-standard sequencing. Any positive samples will also be confirmed as per standard clinical pathways. Any divergence between the POCT and gold-standard methodology will be reviewed by the trial management committee.

Data collection will be undertaken contemporaneously by the clinical staff and any missing data will be collected by the NICU research nurses. Data will be entered into an electronic database by the clinical team and a study ID will be generated. The participants will subsequently be anonymised to the research team. If an individual is not tested for any reason (eg, test overlooked, staff availability or the individual meets the exclusion criteria), these incidences will be captured retrospectively by NICU research nurses by checking daily admission records and the reasons will be documented.

### Samples size

The sample size (approximately 900 babies) is estimated based on the expected number of admissions across both clinical sites over an approximate 10-month trial period. To achieve a statistical power of 90% with a 5% significance level, a margin of 0.5 (in Cohen’s d, which equates to about 7 min difference given the SD in the control sample) and a control sample of N=50, a test sample size of 112 is required. With the forecast test sample size of 900, statistical power should be around 95% to detect variance in clinical timings before and after implementation.

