### Secondary outcomes

This trial will also assess several secondary outcomes including the total number of neonates identified with the m.1555A>G genetic variant (positive result) as a proportion of the study population. An assessment of resource impact will be undertaken, including a health economic analysis of additional staff time to secure sample and testing and costs associated with alternative antibiotic prescribing for any positive tests. We will record the number of neonates where testing was not undertaken and the rationale for this. Correlation of the POCT result with the current in-house reference assay will be assessed and any test fails will be reported. In the acute neonatal setting, delivering antibiotics in a timely manner is critical and this should ideally be within an hour after admission. As such, we will assess whether the time to antibiotic administration after admission is impacted by implementation of the genetic POCT. A reference time to antibiotic was measured over a month-long period before implementation.

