### Inclusion criteria

All babies admitted to NICU across the two participating sites, commencing from the trial start date. This includes babies admitted directly from delivery suite, midwifery led units or transferred from another neonatal unit. At the LWH site, babies who are screened for infection on the NICU but then transferred to external wards (not formally admitted to NICU) will also be included. It is a clinical decision whether the babies are being screened for infection as part of their assessment, reflecting the real-world, pragmatic, nature of the trial. This also reflects the variation in admission procedures between the two trial sites where pathways differ due to local practices.

Given that all babies admitted to NICU are eligible for recruitment, some of those recruited will not go onto receive antibiotic therapy. If the baby did not go onto receive antibiotics, their data will still form part of the dataset for analysis.

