### Statistical analysis

For the primary outcome, simple descriptive statistics will be used to provide a metric for the proportion of babies tested for the variant over the number who were ultimately prescribed aminoglycoside antibiotics.

Regarding the secondary outcome measures, the objective is to establish that the introduction of the POCT does not significantly impact the time between admission to NICU and the prescription of antibiotics for acute admissions. For the purposes of this analysis, those babies receiving antibiotics within the first 2 hours of admission, representing acute antibiotic administration, will be compared. The burden of proof rests on the research hypothesis, meaning the null hypothesis is that the new POCT does impact this quantity. This is a so-called non-inferiority significance test. The quantity of interest is the mean difference between the admission to ICU and prescription of antibiotics timestamps in two situations: with and without the POCT test 
$\left(\mu_{c},\mu_{t}\right)$
. The null hypothesis is that the difference between these quantities is greater than or equal to some prespecified margin 
(Δ)
 that is, 
$H_{0}:\mu_{c}-\mu_{t}\geq \Delta ;H_{A}:U_{t}-U_{c}<\Delta$
. A type I error here is concluding the time durations are equivalent when in fact the time to antibiotic with the POCT is greater.

The two samples are of unequal size, with the control (‘before implementation’) sample having about 
$n_{c}$
=50, and a forecasted test sample size of around 
$n_{t}$
=900. We also have no insight into population variance and cannot assume they are the same in both groups (it may eg, take some staff members longer to carry out the new test than others). As such, a one-sided Welch t-test will be used to reject or not reject the null hypothesis.

Throughout the study we anticipate that there will be iterative updates to the POCT technology, as avenues for optimisation emerge because of our findings from real-world implementation. The timings of these updates will be recorded and separate post-hoc statistical analysis will be undertaken to assess the impact of each update.

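### The timing test's stated test sample of about 900 is the forecast of all admissions, but only babies given antibiotics within 2 hours are analysed; the power figure largely survives

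*Protocol article*

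**What the plan says.** The protocol article's section on sample size says the figure of about 900 is "estimated based on the expected number of admissions across both clinical sites over an approximate 10-month trial period". It then sets the design for the timing comparison: 90% power, 5% significance, a margin of 0.5 in Cohen's d (about 7 minutes), 50 controls, and 112 test babies required. It closes with "With the forecast test sample size of 900, statistical power should be around 95" per cent.

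The statistical analysis section names the test ("a one-sided Welch t-test will be used to reject or not reject the null hypothesis") and gives the two sample sizes as about 50 controls and about 900 test babies. The same section defines who enters the comparison: "those babies receiving antibiotics within the first 2 hours of admission, representing acute antibiotic administration, will be compared".

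The inclusion criteria admit every baby admitted to the units and note that "some of those recruited will not go onto receive antibiotic therapy". The secondary outcomes section describes the control data: "A reference time to antibiotic was measured over a month-long period before implementation".

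**The concern.** The 900 is a count of admissions, while the timing test runs on a subset of them. Babies who receive no antibiotics, or who first receive them more than 2 hours after admission, are recruited but do not enter the comparison. A number forecast for the whole cannot also be the number in the part, so the test sample attached to the power statement is one the design cannot deliver.

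This is the only formal hypothesis test in the document, since the primary outcome is purely descriptive. It carries the claim that the point-of-care test does not delay antibiotics. A reader judging that claim should see the number of babies it will rest on. The question is then whether the stated power still holds once the right number is used.

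**Working it through.** **Inputs.** From the sample size section: 5% significance, 90% target power, margin 0.5 SD, 50 controls, 112 test babies required, 900 forecast. From the statistical analysis section: one-sided Welch test, restricted to babies given antibiotics within 2 hours. Assumed: true difference zero and, at first, equal SDs. The share of admissions that meets the 2-hour rule is not given, so it is varied.

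**Formula.** Let r be the test-period SD divided by the control SD. In control-SD units:

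- standard error: se = √(1/n_c + r²/n_t)
- noncentrality: λ = 0.5 / se
- degrees of freedom: ν by Satterthwaite (Welch), or n_c + n_t − 2 (pooled)
- power = P(T > t₀.₉₅,ν), with T noncentral t on ν degrees of freedom with noncentrality λ

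**Step 1: reproduce the plan's figures.**

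- 50 vs 112, pooled: se = √(0.02 + 0.00893) = 0.1701, λ = 2.940, ν = 160, power 90.0%. The plan's 112 is reproduced exactly. Under Welch the power at 112 is 89.9%, and 115 babies are needed for 90%.
- 50 vs 900, Welch: se = √(0.02 + 0.00111) = 0.1453, λ = 3.441, ν = 54.6, power 96.0%. This agrees with the stated figure of around 95%.
- Two-sided versions do not give 112 (274 pooled, 324 Welch), so the plan's calculation was one-sided at 5%.

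The arithmetic is sound for the inputs used. What is wrong is the input of 900.

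**Step 2: replace 900 by a subset.** Welch power with 50 controls:

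| Share of 900 analysed | n_t | Power, equal SDs | Power, test SD 1.5 times larger |
|---|---|---|---|
| 100% | 900 | 96.0% | 95.1% |
| 50% | 450 | 95.3% | 93.2% |
| 40% | 360 | 94.9% | 92.2% |
| 20% | 180 | 92.7% | 86.7% |
| 12.4% | 112 | 89.9% | 80.0% |

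The last column is included because the statistical analysis section says equal variances cannot be assumed. The margin there stays at 0.5 of the control SD.

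**Step 3: why power moves so little.** With 50 controls the term 1/50 = 0.02 dominates the standard error. At n_t = 900 the test arm adds 0.0011, and at 450 it adds 0.0022. Even with unlimited test babies, λ = 0.5 × √50 = 3.536 on 49 degrees of freedom gives 96.7%. Beyond a few hundred babies, the test sample hardly matters.

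**The case against.** The strongest reply is that nothing practical changes. The plan itself says 112 test babies are enough, its arithmetic reproduces, and power with 50 controls stays near 95% until the analysed share falls below about 40% of admissions. The outcome is secondary and recruitment has closed. All of this stands, and it is why the point is minor. It does not remove the point, because a stated sample size contradicts the analysis set defined beside it. Nor is this detail that a condensed article may leave to a fuller document, since the article itself gives the number and the restriction.

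A reader might infer two stronger claims, and the documents support neither.

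- **That the true test sample is about 500.** This comes from 900 / 10 = 90 admissions a month set against about 50 controls in one reference month, so 50/90 = 56% and 0.56 × 900 ≈ 500. It requires the 50 to be every eligible baby at both sites in that month, already restricted to 2 hours, with the same monthly throughput later. The document says none of this. Even at 500, power would be 95.4%.
- **That the 2-hour rule also cuts the controls and leaves the test underpowered.** Applying the 56% share to both groups gives 28 vs 500 and 80.8% power. But 50/90 is a filter share only if the 50 are already filtered, and then they cannot be filtered again. The plan's own SD also weighs against heavy loss of controls. Seven minutes at 0.5 SD implies an SD of about 14 minutes. If that SD describes all 50 and a share p of them exceeds 120 minutes, Cantelli's inequality requires a mean of at least 120 − 14√((1−p)/p). Keeping 40 of 50 (p = 0.2) gives 120 − 14 × 2 = 92 minutes; keeping 28 (p = 0.44) gives about 104 minutes. The secondary outcomes section says antibiotics should ideally be given within an hour, so such means look unlikely. This argument fails only if the SD was computed after the restriction while the 50 were counted before it, and nothing in the text suggests that.

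**Conclusion.** The point holds as a mismatch between a stated sample size and the analysis set. About 900 is a forecast of admissions; the Welch test will use a smaller number, by an amount that cannot be derived from the document.

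The stated power of around 95% survives over a wide range. With equal SDs it is 94.9% or more down to 360 analysed babies, and it falls below 90% only near the 112 that the plan itself requires. With a test-period SD 1.5 times the control SD, power is 92.2% at 360 and 86.7% at 180, so it crosses 90% between those numbers. These figures assume 50 analysed controls, a zero true difference and a margin of 0.5 control SD. On that basis the test is not shown to be underpowered. This is a minor correction for a secondary outcome.

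**What to change.** In the sample size section, keep about 900 as the recruitment forecast only. There and in the statistical analysis section, restate the test sample for the timing comparison as the forecast number of babies given antibiotics within 2 hours of admission. Count the 50 controls on that same set, and quote the Welch power for that pair of numbers. If the proportion meeting the 2-hour rule was not known at planning, give a short range such as the table above, including a row or column for unequal SDs.

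The cost is a change of wording and one recalculation. No more babies are needed and no clinical procedure changes. Recruitment has closed but analysis is described as ongoing, so the clarification can still accompany the results.

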### Statistical analysis

For the primary outcome, simple descriptive statistics will be used to provide a metric for the proportion of babies tested for the variant over the number who were ultimately prescribed aminoglycoside antibiotics.

Regarding the secondary outcome measures, the objective is to establish that the introduction of the POCT does not significantly impact the time between admission to NICU and the prescription of antibiotics for acute admissions. For the purposes of this analysis, those babies receiving antibiotics within the first 2 hours of admission, representing acute antibiotic administration, will be compared. The burden of proof rests on the research hypothesis, meaning the null hypothesis is that the new POCT does impact this quantity. This is a so-called non-inferiority significance test. The quantity of interest is the mean difference between the admission to ICU and prescription of antibiotics timestamps in two situations: with and without the POCT test 
$\left(\mu_{c},\mu_{t}\right)$
. The null hypothesis is that the difference between these quantities is greater than or equal to some prespecified margin 
(Δ)
 that is, 
$H_{0}:\mu_{c}-\mu_{t}\geq \Delta ;H_{A}:U_{t}-U_{c}<\Delta$
. A type I error here is concluding the time durations are equivalent when in fact the time to antibiotic with the POCT is greater.

The two samples are of unequal size, with the control (‘before implementation’) sample having about 
$n_{c}$
=50, and a forecasted test sample size of around 
$n_{t}$
=900. We also have no insight into population variance and cannot assume they are the same in both groups (it may eg, take some staff members longer to carry out the new test than others). As such, a one-sided Welch t-test will be used to reject or not reject the null hypothesis.

Throughout the study we anticipate that there will be iterative updates to the POCT technology, as avenues for optimisation emerge because of our findings from real-world implementation. The timings of these updates will be recorded and separate post-hoc statistical analysis will be undertaken to assess the impact of each update.

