The m.1555A>G variant is strongly associated with AIO and has a reported prevalence of 0.2% (~1 in 500).^7^ It has previously been suggested that genetic testing should be used in children requiring aminoglycosides to prevent hearing loss and that this approach would be cost-effective when balanced against the costs of lifelong deafness.^3 7^ In many centres, children with cystic fibrosis are tested for the variant at diagnosis as it is expected that these individuals will require aminoglycoside antibiotics at some stage in their lives. This is typically undertaken by a validated genotyping assay in an accredited diagnostic laboratory, a strategy which takes approximately 3–4 days to return a result. Understandably, this testing strategy is not suitable for use in clinical settings where administration of antibiotics is required within an hour of the decision to start treatment with antibiotics.

Currently, there is an inability to test for the m.1555A>G variant in the acute setting such as babies admitted to the neonatal intensive care unit (NICU), representing approximately 90 000 admissions per year in the UK alone. By introducing a simple genetic point of care test (POCT) with a result in under 30 min, we have the potential to avoid approximately 180 cases of severe/profound irreversible deafness every year in the UK alone. Those babies with the m.1555A>G variant could be prescribed an equally effective second line antibiotic, such as a cephalosporin. The UK NICE guidance for early onset neonatal infection recommends a combination of gentamicin and benzylpenicillin as first-line therapy not due to superiority over other agents on an individual patient level, but because that regimen has a narrower spectrum of activity and therefore does not readily contribute towards the development of resistant bacterial pathogens.^4^

Alongside an industry partner, genedrive, we have a developed a small and robust thermocycler platform for rapid point-of-care diagnostic testing of the m.1555A>G variant which has been CE certified for clinical use. This protocol describes a multi-centre prospective observational trial to assess the implementation of the POCT in the clinical setting.

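### The timing outcome is stated as admission to antibiotic administration but tested as admission to prescription, so the test cannot see a dose held after the prescription is written

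*Protocol article*

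**What the plan says.** All references are to the Protocol article.

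- **Secondary outcomes** gives the timing outcome: "we will assess whether the time to antibiotic administration after admission is impacted by implementation of the genetic POCT". The reason given is that prompt delivery of antibiotics is critical in this setting. The reference interval from the month before implementation is described only as a time to antibiotic, with no end event named.
- **Statistical analysis** gives the objective as showing that "the introduction of the POCT does not significantly impact the time between admission to NICU and the prescription of antibiotics for acute admissions". It then defines the estimand in the same terms: "The quantity of interest is the mean difference between the admission to ICU and prescription of antibiotics timestamps in two situations". Prescription as the end event is therefore stated twice.
- **Statistical analysis** also defines the analysis set by receipt of the drug: "those babies receiving antibiotics within the first 2 hours of admission, representing acute antibiotic administration, will be compared".
- **Testing process and assessment** (text below Figure 1) lists the recorded variables. The list starts with demographics and admission time and ends with "time of assay result, assay result, time of antibiotic prescription, antibiotics prescribed". Administration time is not on it.
- **Testing process and assessment** sets a separate clock start: "the time that a decision was made to prescribe antibiotics represents time 0". Admission is used only when no antibiotic is prescribed.
- **Background** counts the one-hour expectation from the decision ("administration of antibiotics is required within an hour of the decision to start treatment with antibiotics"), while Secondary outcomes counts it from admission.

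**The concern.** Prescription and administration are different events, and the clinical question is when the baby receives the drug. The outcome section asks about administration, and the analysis section answers for prescription. As listed, the data would not allow the stated outcome to be computed, or the 2-hour analysis set to be selected by receipt of the drug.

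This comparison is the article's only formal hypothesis test. It is also the only formal check on the part of the primary objective that concerns leaving standard care undisturbed. A non-inferiority result on prescription time could be read as evidence that doses were not delayed, which that test would not show.

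**Working it through.** **Step 1. Compare the definitions.**

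| Place | Start | End |
|---|---|---|
| Secondary outcomes | admission | administration |
| Statistical analysis, objective and estimand | admission | prescription |
| Statistical analysis, 2-hour set | admission | receipt of antibiotics |
| Variable list below Figure 1 | admission and decision times both listed | prescription listed, administration not listed |
| Reference month | not restated | time to antibiotic, event not named |

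The start agrees between the outcome and the analysis. The end does not.

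**Step 2. Where a wait for the result would fall.** Write the admission-to-administration interval as A = P + G, where P is admission to prescription and G is prescription to dose. The test uses P only.

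- If the prescriber waits for the result, the wait lies in P and the test sees it.
- If the prescription is written and the dose is held, the wait lies in G and the test does not see it.

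Testing process and assessment says the result can inform prescribing once available, but sets no rule that the prescription must wait for it. Both orders are possible.

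**Step 3. Reproduce the plan's own figure.** Inputs from Samples size and Statistical analysis: d = 0.5, control n = 50, power 90%, 5% level, one-sided test. With equal SDs and a true difference of zero, the noncentrality is d / √(1/50 + 1/n).

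- At n = 112: 0.5 / √(0.02 + 0.00893) = 2.94. The one-sided pooled t-test has power 0.900, and 112 is the smallest n reaching 90%. The stated figure reproduces.
- At n = 900: power is 0.960 (Welch) to 0.964 (pooled t), against a stated value of around 95%.

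The margin of d = 0.5, equated to about 7 min, implies an SD of about 7 / 0.5 = 14 min. No stated figure is wrong on this point.

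**Step 4. Size of a hidden delay, for illustration.** The Abstract gives an assay time of 26 min. If a share s of babies has the dose held for one full run after prescription, mean A rises by 26s while mean P is unchanged. Setting 26s = 7 gives s = 7/26 = 0.27.

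**Step 5. What each test would conclude.** Assumptions: SD 14 min for either interval, margin 7 min, n = 50 and 900 (the plan's forecast), normal approximation.

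SE = 14 × √(1/50 + 1/900) = 2.03 min. P(declare non-inferiority) = Φ((7 − delay)/2.03 − 1.645).

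| True mean delay, all of it after prescription | Test on administration | Test on prescription |
|---|---|---|
| 0 min | 96% | 96% |
| 3 min | 63% | 96% |
| 7 min | 5% | 96% |
| 10 min | 0.1% | 96% |

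**Step 6. Power if the endpoint is changed.** The SD of admission to administration is not given. With a 7-minute margin, no true delay and the same sample sizes, power = Φ(7 / (SD × 0.1453) − 1.645), where 0.1453 = √(1/50 + 1/900):

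- SD 14 min: 96%
- SD 20 min: 78%
- SD 28 min: 53%

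**The case against.** Several arguments limit this point.

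- **The masking is conditional.** The pathway describes the result as feeding into prescribing, and decision time is recorded separately from prescription time. If staff wait for the result before prescribing, the tested interval contains the wait. A reader might infer that the endpoint shows no delay by construction. That holds only when the prescription is written first and the dose is then held, and the document does not say how often this happens.
- **The two periods may well record the same event.** A reader might infer that the control month timed administration and the POCT period timed prescription, which would favour the POCT by the prescription-to-dose gap. The Statistical analysis section defines one quantity for both situations, and nothing shows that the control month measured another. The loose description of the reference interval leaves this open but does not establish it.
- **The clock start is not an endpoint conflict.** A reader might see two competing clocks. The outcome and the analysis both count from admission, and the decision-based time 0 is tied to no stated analysis. The one-hour statements are a background remark and an ideal, not analysis thresholds.
- **The variable list may be incomplete.** It omits items collected elsewhere, such as reasons for not testing and adverse events, and a condensed article need not reproduce the data form. Administration time may therefore exist, and the 2-hour set suggests that it might.
- **The 27% is arithmetic only.** It counts the whole run as added delay, although the swab is taken alongside normal admission procedures.

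All five stand as limits. None removes the core: even if administration time is held, the article states one end event for the outcome and a different one, twice, for the test. That is a contradiction in what the article chose to state, not detail left to a fuller document.

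**Conclusion.** The point holds in this form: the stated outcome ends at administration, the tested quantity ends at prescription, and the listed data support only the latter. Non-inferiority on prescription would not show that administration was not delayed, because any wait between prescription and dose lies outside the tested interval.

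The possible size is material against the margin. A full-run wait in about 27% of babies would equal it. With a true 7-minute delay lying wholly after prescription, the prescription test would still pass about 96% of the time, against 5% for a test on administration. These figures assume an SD of 14 min, the forecast of 900 and a delay entirely after the prescription. They illustrate what the test could miss and do not estimate what occurred.

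The documents do not support saying that a delay was masked or that the two periods timed different events. The point should be fixed, but it ranks below the most serious class because the comparison is a secondary outcome and the primary outcome is a descriptive proportion.

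**What to change.** 1. Make the tested endpoint admission to antibiotic administration, as Secondary outcomes already states, with one definition for the control month and the POCT period.
2. Take administration time from the drug charts. Specify that it refers to the aminoglycoside, or to the antibiotic given in its place. First-line therapy at both units combines a beta-lactam with an aminoglycoside, so timing the first dose of any antibiotic could let an earlier beta-lactam dose hide a delay in the drug that the test bears on.
3. Recheck the 7-minute margin and the power against the SD of the new interval.
4. Report admission to prescription as supportive.
5. If administration times cannot be recovered for both periods, state that the test concerns prescription only and draw no conclusion about administration.
6. As a minor point, reconcile the decision-based time 0 and the two one-hour statements (Background and Secondary outcomes) with the admission-based clock.

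The cost is one chart timestamp per baby in both periods, plus a margin and power recheck that may give a less favourable figure. Trial status says recruitment has closed and analysis is ongoing, and participants are anonymised to the research team, so retrieval would have to go through site staff. The wording can still be aligned before results are reported.
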